### Sample size

As this study is being conducted in the context of an outbreak, in which the study aims to generate as much information as possible about a disease that has previously been poorly characterised, no target sample size has been pre-defined for the purpose of the analysis, which is primarily descriptive.

However, in order to satisfy regulatory requirements, the study has been approved to enrol a maximum of 1,400 participants.

### Study setting

Participants are enrolled in secondary care settings across Europe and in Singapore, and may be managed as either inpatients or outpatients. Other countries may be added to the study as the outbreak evolves.

### Eligibility criteria

**
*Inclusion criteria*
**

1. Patients with:a. Laboratory confirmed mpox virus diseaseb. Laboratory confirmation pending, but who are being managed as a presumptive case

2. Informed consent provided for participation in the study

A presumptive case is defined as a patient who is managed as a case of mpox due to high clinical suspicion of disease (according to
the prevailing World Health Organization (WHO) case definition) or high risk of serious disease (such as immunosuppression). A patient who is a presumptive case and subsequently tests negative for MPXV exits the study.

No exemptions are made regarding eligibility. Each participant must satisfy all the approved eligibility criteria.

**
*Exclusion criteria*
**

1. Presumptive cases with a subsequent negative test for MPXV2. Adults lacking capacity due to a previously diagnosed impairing condition3. In Tier 2 and Tier 3 in France only: participants under the age of 18 years4. In Singapore only: participants under the age of 21 years and adults who lack capacity to provide written informed consent for themselves

### Recruitment

Participants are enrolled in the study before laboratory confirmation of mpox on the basis of high clinical suspicion or at any time after they receive a positive diagnosis of mpox infection by PCR. From June 2022 to December 2022, new cases were recruited prospectively from participating sites that had been activated. Then, from January 2023, as new cases were rare, patients managed before the start of the study at participating sites or patients from newly activated sites were recruited retrospectively.

Potential participants are identified and approached to participate in this study by their clinical care team at a participating site. Identification may take place using the Site Investigator’s patient register. The Site Investigator must, in all cases, confirm that the potential participant meets the eligibility criteria before proceeding further with the inclusion process. Any patient meeting the inclusion criteria can be enrolled in the study whether they are currently managed or have previously been managed as a mpox case, provided they give their informed consent to participate.

If the potential participant meets all the eligibility criteria, information about the study is provided using the participant information sheet. The participant information sheet can be given in person during a clinic visit, or in the event that the patient is currently being managed as an outpatient and has no upcoming scheduled clinical visit, the information sheet can be sent by post or email, or it can be explained by telephone
(according to the site’s locally approved practices).

The participant information sheet details no less than: the nature of the study; what it involves for the participant; the implications and constraints of the protocol; and any risks involved in taking part. It is clearly stated that the participant is free to withdraw from the study at any time for any reason without prejudice to future care, without affecting their legal rights or their care and with no obligation to give the reason for withdrawal.

The participant is permitted as much time as desired to consider the information, and given the opportunity to question the Investigator, their doctor or other independent parties to decide whether they participate in the study.

Participation is entirely voluntary.

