### Participant timelime

Enrolment is the day that the informed consent form is signed, and the participant is enrolled in the study. Enrolment may be any day once the diagnostic sample is taken or after the patient has been considered a “presumptive case” by their treating clinician.

After enrolment, days are counted from the date the diagnostic sample is taken:

Day 1 is the date that the first sample to diagnose mpox was taken, regardless of when results became available. If the participant is enrolled on the same day that the diagnostic sample is taken, enrolment occurs on Day 1.If a participant is enrolled after the date that the diagnostic sample was taken, then study procedures start from the number of days since the sample was taken.

Participants who do not receive treatment follow the schedule from D1 and continue until D180. Participants who receive treatment immediately following diagnosis and enrolment in the study follow the schedule described above.

If a participant enters the study without receiving treatment and then begins receiving treatment at a later date, they initiate a new schedule of procedures by restarting at D1. This second D1 represents the date of treatment start. This extends the study participation period by the number of days between enrolment and treatment initiation.

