1&2	HIV-RNA quantification						X		X
1&2	MPXV quantification (sPCR) + infectivity assessment (cell culture)	X	X	X	X	X	X	X	X
1&2	MPXV sequencing	X	X	X	X	X	X	X	X
1&2	Humoral immune response characterisation (anti- MPXV antibodies quantification, seroneutralization)						X		
1&2 &3	Cellular immune response characterisation						X		
1&2	Genetic host factors determination + auto-immune antibodies detection						X		
1&2	Tecovirimat pharmacokinetics						X		

HIV, human immunodeficiency virus; MPXV, mpox virus.

Please refer to ‘Additional File 2: Appendix F’ in
*Extended data* for further information on sample processing, analysis and storage in the UK
^
7
^.

**
*Participant self-assessment survey.*
** All participants are asked to complete a self-assessment survey from the point of entry into the study until D180
*via* a secure online questionnaire. The questionnaire, completed
*via* online REDCap survey, captures information about the participant’s signs and symptoms, including lesion status.

For Tier 2 and Tier 3 in France, the baseline self-assessment survey includes an additional social and sexual behaviour questionnaire.

**
*Outcome assessment.*
** During the medical assessment on D14, 28, 60 and 180, the clinical status according to a four-point ordinal scale (see the
*Outcomes* section) is recorded.

For participants who are pregnant at any time during the study, they are followed in the study until their pregnancy outcome is known.

*Note:* As participants can consent to enrol in the study at any point after receipt of a positive PCR result for mpox infection, the eCRF can be completed using existing medical notes and results of samples already taken.

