### Statistical method

**
*Sample size.*
** This is an observational study. We are interested in the effect of any available treatment against mpox used in the cohort and thus defined treatment outcomes (see below). However, due to the observational nature of this study, there is no formal sample size calculation to assess treatment effect. The availability of treatments and prescription rules differ in time and across countries. Any causal inference analysis will account for confounding effects, pre-specified in the statistical analytical plan.

**
*Participant flowchart.*
** The total number of patients and the flowchart of the study will be presented with the number of patients excluded (with reasons for exclusion, and number of patients for each reason), included, receiving any antiviral drugs, lost-to-follow-up and analysed.

**
*Descriptive statistics.*
** Patients’ demographics and baseline characteristics will be described overall and across analysis groups (
*e.g.*, treated with and without tecovirimat), by using, for continuous variables: sample size, mean, standard deviation, median, interquartile range, minimum and maximum; and for categorical variables: sample size, proportion and number of patients in different categories.

The number of missing values, overall and per group, will be reported.

**
*Inferential statistics.*
** Causal inference methods will be used to derive information on the effects of tecovirimat (or other antiviral drugs) on patients’ outcomes (see below) and assessed from a Cox proportional hazard model. Graphics and tables associated to the analysis of each outcome will be fully detailed in the SAP.

**
*Primary outcome.*
** The time to lesion resolution will be summarized for the overall population and stratified by treatment status using Kaplan-Meier curves, median time-to-event, proportion of resolution at D14, and associated 95% confidence intervals (CIs).

**
*Secondary outcomes.*
** For clinical status at D14 and D28, counts and percentages will be presented with their associated 95% CI. The four-point ordinal scale will be used to estimate a proportional odds model. Recrudescence or relapse will be compared between treatment status with a logistic regression model.

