### Statistical method

**
*Analysis population.*
** All eligible participants will be included in the final analysis,
*i.e.*, the final analysis set will be the overall population of enrolled participants (prospective and retrospective, with positive mpox PCR).

**
*Method to account for missing, unused or invalid data.*
** The number, timing and pattern for missing values will be detailed for each outcome measure. For missing primary time-to-event outcome:

The patients who are lost to follow-up or withdrew from the trial and who did not experience the event will be censored at their lost to follow-up or withdrawal datePatients who died before experiencing the event will be censored at day 14If the patient is hospitalized, the event will be censored at hospital discharge day, whereas if the patient is an outpatient, the event will be censored at the last available date in the medical assessment formsIf the outcome is still missing, it will be searched in the Patient Self-Assessment Surveys (PSA)

For the four-point clinical scales at day 14 and day 28, missing data will be imputed by using the last observation carried forward (LOCF) method for “Death” and “All lesions are completely resolved and no serious complications” modalities. Missing outcomes will be searched as done for the primary endpoint.

Endpoints still missing after these recovery steps will remain missing in the analyses.

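### Participants enrolled after D14 or D28 cannot be counted as deaths at that day but stay in the denominator, so the planned mortality interval looks more precise than it is

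*Protocol article*

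**What the plan says.** All of the following is in the protocol article.

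- **Consent.** Eligibility criteria lists "Informed consent provided for participation in the study" as an inclusion criterion and adds: "No exemptions are made regarding eligibility. Each participant must satisfy all the approved eligibility criteria".
- **Past cases.** Recruitment admits patients "whether they are currently managed or have previously been managed as a mpox case, provided they give their informed consent to participate". It reports that from January 2023 "patients managed before the start of the study at participating sites or patients from newly activated sites were recruited retrospectively".
- **Time origin.** The participant timeline section states: "Day 1 is the date that the first sample to diagnose mpox was taken, regardless of when results became available". A participant who starts treatment later restarts at a new D1 on the treatment start date. In neither case does the clock start at consent.
- **Source of outcomes.** For people who consent late, Data collection methods says that "the eCRF can be completed using existing medical notes and results of samples already taken".
- **Outcome.** Under Outcomes, the fourth level (d) of the ordinal scale at D14 and D28 is death.
- **Analysis.** Statistical method, Secondary outcomes: "For clinical status at D14 and D28, counts and percentages will be presented with their associated 95% CI".
- **Analysis set.** Statistical method, Analysis population: "the final analysis set will be the overall population of enrolled participants (prospective and retrospective, with positive mpox PCR").

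The only split of results that the article names is by treatment status. It names none by recruitment mode or by enrolment date.

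**The concern.** A person who consents after D28 has survived both assessment days, and one who consents between D14 and D28 has survived D14. For these people level d is a structural zero: it could not have been observed, whatever the true risk. Counting them as non-deaths adds to the denominator without adding information on mortality. The death percentage is pulled towards zero and its interval narrows.

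The study is described as primarily descriptive, so percentages and intervals are its main product. If no deaths are seen, the upper limit is all that the D14/D28 tables say about mortality, and a reader would take it as resting on every participant having been at risk of being counted as dead.

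**Working it through.** The article states no mortality estimate or interval, so there is no figure of its own to reproduce.

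**Inputs**

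- N = 601 PCR-confirmed participants enrolled (Discussion).
- 95% confidence level (Statistical method). The interval method is not named; the exact Clopper-Pearson interval is assumed, with Wilson as a check.
- Outbreak fatality below 0.01% (Background and rationale).
- f, the share enrolled after the assessment day. It is not in the article, so it is an assumption, varied from 10% to 75%. It differs by day: everyone enrolled after D28 was also enrolled after D14, so f at D14 is at least f at D28.

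**Step 1: point estimate.** With d deaths, the pooled percentage is d/N. Only n = (1 − f)N participants could have been observed to die, so the percentage among them is d/[(1 − f)N]. The pooled figure is (1 − f) times that. For example, 2 deaths give 2/601 = 0.33% pooled (exact interval 0.04% to 1.20%). At f = 50% they give 2/300 = 0.67% (0.08% to 2.39%).

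**Step 2: upper limit with no deaths.** The exact two-sided 95% upper limit for 0/n is 1 − 0.025^(1/n), which is close to 3.69/n. The ratio of the at-risk limit to the pooled limit is therefore about N/n = 1/(1 − f).

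| f (assumed) | n at risk | Upper limit | Ratio to pooled |
|---|---|---|---|
| 0 (pooled, as planned) | 601 | 0.61% | 1 |
| 10% | 541 | 0.68% | 1.11 |
| 25% | 451 | 0.81% | 1.33 |
| 50% | 300 | 1.22% | 2.00 |
| 75% | 150 | 2.43% | 3.97 |

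The Wilson limits are 0.64% pooled and 1.26% at f = 50%, so the choice of interval method does not matter here.

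**Step 3: does the pooled interval still cover?** At a fatality of 0.01%, expected deaths are 601 × 0.0001 = 0.06, so zero deaths is by far the likeliest result. The pooled upper limit is never below 0.61%, so a true mortality under that cannot be missed from above. Exact coverage, with deaths binomial in the n at risk, is above 95% at each of the values 0.01%, 0.1% and 0.5%, for every f tried (0, 25%, 50% and 75%). At a true mortality of 1% it is 96% for f = 0, 94% for 25%, 80% for 50% and 44% for 75%.

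**Step 4: what the simple correction leaves.** Someone enrolled on day 10 could not have been seen to die on days 1 to 9, yet remains in the D14 denominator after the correction. The at-risk limits above are therefore themselves slightly too low.

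**The case against.** The strongest reply is that nothing goes wrong at the article's own fatality. Below 0.01%, expected deaths are about 0.06, the percentage will almost surely be zero either way, and the pooled limit of 0.61% is some 60 times the stated rate. Coverage fails only at a mortality near 1% or above. The article gives values of that size for earlier Clade II outbreaks in Africa (1.7 to 6.8%), not for this one. This stands, and it limits the point to precision. It does not remove the point: the upper limit would still claim more information than the data hold.

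Second, f is unknown. At 10% the limit moves only from 0.61% to 0.68%. That also stands. The 122 cases of the early partial report should not be used as the number at risk, because the article does not say that this is how many enrolled before D14 or D28.

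Third, details are left to a SAP that is not shown, and an overall analysis set does not forbid an outcome-specific denominator. That is true, but the article does more than stay silent: it fixes a pooled set for the final analysis. A SAP that follows it as written repeats the problem.

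Fourth, proxy consent might let deaths in. The section on who takes consent refers to an appendix, not shown, for children, people unable to write and adults lacking capacity. Nothing in the article provides for enrolling people who had died.

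A reader might infer that fatal SAEs are a structural zero in the same way. The documents do not support this. Outcomes and Statistical method count SAEs over 28 days starting at enrolment, so a death after a late consent can be counted. Harms collects from the diagnostic sample (or enrolment, if earlier) to D28, which is a different window. In any case only the number and type of events are to be described; no percentage or interval is planned.

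**Conclusion.** The point holds as one of overstated precision on mortality at D14 and D28. Consent without exemption, retrospective enrolment, a clock that starts before consent and a pooled analysis set together put people who could not have been recorded as dead into the denominator. The death percentage is too low by the factor 1 − f, and the upper limit is too low by a factor of about 1/(1 − f). With no deaths that means 0.61% where 0.68% to 2.43% would be justified, for f between 10% and 75%.

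The size rests on an assumed f, on an exact interval and on the 601 enrolled at the time of writing. A reader might go further and infer that the study will report a materially wrong death rate, or an interval that misses the truth. At the fatality stated for this outbreak, neither follows.

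**What to change.** In Statistical method (Secondary outcomes and Analysis population), and in the SAP, state that the level d percentage and its 95% confidence interval at D14 and at D28 are computed only in participants enrolled before that day, with that denominator shown. Report the scale for later enrolees separately, as levels a to c conditional on survival to consent. Add a note that participants enrolled some days after Day 1 carry a smaller residual bias, which an analysis with delayed entry at consent would remove.

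Enrolment is defined as the day the consent form is signed, so the date needed is already recorded. The cost is a change of wording and one extra denominator per assessment day; no new follow-up is needed. The downside is a wider, less favourable mortality interval. Counting patients on site registers who died before they could be approached is not part of this change: it would need new data from the sites on people who never consented.

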### Who takes informed consent?

Consent is taken by the patient’s clinical management team based at the health facility in which their mpox illness is currently or was formerly being managed.

The participant enrolled during a clinic visit must personally sign and date the latest approved version of the Informed Consent form before any study specific procedures are performed.

For participants who are being managed as outpatients and do not have a scheduled clinic visit, consent can be obtained by phone, post or e-signature (according to the recruiting site’s local practices and approvals).

The person who obtained the participant’s consent in person or remotely must be suitably qualified and experienced, and have been authorised to do so by the Principal Investigator (PI). A copy of the signed informed consent form is given to the participant. An original signed form is retained at the study site.

In the UK, at sites participating in both MOSAIC and the UK Clinical Characterisation Protocol (UK CCP), participants can be co-enrolled in both studies.

Specific document and consent procedures are in place for consent of vulnerable population. Please see ‘Additional File 2: Appendix B’ in
*Extended data*
^
7
^ for the consent process for children, participants who are unable to write, and adults who lack capacity to provide consent for themselves.

At the start of the study, consent was not required in France. Pending the EU approval, the French Ethic Committee authorised the study on 27 June 2022 as an observational study or “category 3” study according to the ‘Jardé Law’ for which in accordance with Article L 1122-1 of the Public Health Code, patients may be recruited into the study for data collection only after they have been informed of the purpose, nature, constraints and foreseeable risks of the study and have not objected to the use of their data in this context. Only the investigator must sign and date a no opposition form. On the 17 August 2022, the EU approved the study as a low-intervention clinical trial, so from this date, the study in France follows European requirements and requires signed consent as described in section
*Recruitment* in this protocol.

Please see ‘Additional File 2: Appendix D’ in
*Extended data* for details about taking remote consent in the UK (including phone consent)
^
7
^.

### Additional consent provisions for collection and use of participant data and biological specimens

Optional consent for the use of anonymised samples collected under MOSAIC in future ethically approved research is offered to all participants enrolled in the study.

In France, participants can enrol in Tiers 2 and/or 3 of the study, which explore further virologic and immunological outcomes. A separate participant information sheet and consent form are provided for participants to consider and provide optional consent for these additional study procedures.

### Interventions

This is an observational study. Patients receive standard care as deemed appropriate by the treating physician and depending on availability of approved medications.

### Explanation for the choice of comparators

This is an observational study, there is no control arm.

### Criteria for discontinuing or modifying allocated interventions for a given trial participant

All treatment decisions for discontinuing or modifying treatment are made at the discretion of the patient’s treating physician.

### Strategies to improve adherence to intervention protocols, and any procedures for monitoring adherence

Treatment adherence is monitored by the treating physician as part of routine care.

### Relevant concomitant care and interventions

All concomitant care is given at the discretion of the treating physician.

### Sequence generation

This is not a randomised clinical trial and participants are not randomised to treatment.

### Allocation concealment mechanism

This is not a randomised clinical trial and participants are not randomised to treatment.

### Implementation

This is not a randomised clinical trial. Participants are not randomised to a treatment given at the discretion of the treating physician.

### Blinding (masking)

This is not a blinded study and therefore no-code breaking procedures applies.

